#### Sample size

The primary outcome is the reduction in the abdominal pain intensity in the low-FODMAP diet group compared with the regular diet group over the 4-week intervention. We assumed a 30% difference as being a clinically significant primary endpoint [16]. We estimate that 31 children in each group are needed to achieve a significant difference with a power of 80%, along with a two-sided 5% significance level. Given the anticipated dropout rate of 20%, we estimate 37 subjects are necessary in each study arm. Sample size calculations were performed with StatsDirect (StatsDirect Ltd. StatsDirect statistical software. http://www.statsdirect.com. England: StatsDirect Ltd. 2013).

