**Methods:**

We will perform a randomized, quadruple-blinded, controlled trial. Seventy-four children aged 8 to 18 years with a FAPD (Irritable Bowel Syndrome or Functional Abdominal Pain-Not Otherwise Specified), diagnosed according to the Rome IV criteria, will be randomly allocated to receive either a low-FODMAP diet or a regular diet for 4 weeks. The primary outcome will be the percentage of the responders, defined as the participants who have at least 30% improvement in abdominal pain intensity on a Visual Analogue Scale (VAS) during the last week of the trial compared with baseline, that is at least equal to the Reliable Change Index (≥ 25 mm change on VAS). Other outcomes will include changes in stool consistency, abdominal pain frequency, total scores on the Gastrointestinal Symptom Rating Scale, KIDSCREEN-10 Index and World Health Organization Five Well-Being Index, child’s school attendance and parents’ work absenteeism, and BMI-for-age z-score. Compliance, tolerability of the low-FODMAP diet, and adverse events also will be evaluated. Each FAPD subtype will be assessed separately.

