### Trial design

This study is a single-center, randomized, controlled, quadruple-blinded, superiority trial, with two parallel arms and allocation 1:1, as recommended [16].

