#### Data analysis

All analyses will be conducted on an intention-to-treat basis, including all patients in the groups to which they are randomized for whom outcomes are available (including dropout and withdrawals). Per-protocol analysis also will be performed, in which all subjects who finish the study according to the protocol will be included.

Descriptive statistics will be used to summarize baseline characteristics. The Student t-test will be used to compare mean values of continuous variables approximating a normal distribution. For non-normally distributed variables, the Mann-Whitney U test will be used. The x^2^ test or Fisher exact test will be used, as appropriate, to compare percentages. The same computer software will be used to calculate the relative risk (RR), number needed to treat (NNT), and mean difference (MD), all with a 95% confidence interval (CI). The difference between study groups will be considered significant when the *p* value is < 0.05, when the 95% CI for RR does not include 1.0, or when 95% CI for MD does not include 0. All statistical tests will be two-tailed and performed at the 5% level of significance.

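### The 20% dropout allowance is miscalculated: 31 completers per arm require 39 randomised, not 37

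*Protocol article*

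**What the plan says.** The Sample size section of the protocol article first gives the number needed for analysis: "We estimate that 31 children in each group are needed to achieve a significant difference with a power of 80" per cent, at a "two-sided 5% significance level". It then adds an allowance for attrition: "Given the anticipated dropout rate of 20%, we estimate 37 subjects are necessary in each study arm". The abstract carries the resulting total: "Seventy-four children aged 8 to 18 years with a FAPD". The Trial design section confirms equal arms ("with two parallel arms and allocation 1:1"), so 74 is 2 x 37. The article gives no other dropout rate and no other derivation of 37.

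The Data analysis section defines the main analysis as intention-to-treat, "including all patients in the groups to which they are randomized for whom outcomes are available". The Missing data section adds multiple imputation.

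**The concern.** An allowance for dropout should ensure that the required number remains after the expected losses. Here it does not. Applying the article's own 20% to its own 37 gives fewer than the 31 per arm that it says are needed. The figure looks like the result of adding 20% to the number of completers, rather than dividing by the fraction retained.

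At stake are the recruitment target and the power claim attached to it. If dropout is as anticipated, the stated 80% power is not reached, even when every other assumption in the section is accepted.

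**Working it through.** **Inputs** (Sample size section unless noted)

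- Evaluable children needed per arm: 31
- Power 80%, two-sided significance level 5%
- Anticipated dropout: 20%
- Stated number to randomise: 37 per arm; 74 in total (abstract)
- Allocation 1:1 (Trial design)

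**Step 1. Reproduce the stated figure.** Multiplying by one plus the dropout rate gives 31 x 1.20 = 37.2, which becomes 37 if rounded down. On the total, 62 x 1.20 = 74.4, which becomes 74. The article shows no formula, so this route is inferred, but it does return the stated numbers. Rounding down is a second slip: a minimum sample size is rounded up, which would give 38 even by this method.

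**Step 2. Apply the correct inflation.** With dropout d among those randomised, the number to randomise is n/(1 - d):

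- per arm: 31/(1 - 0.20) = 31/0.80 = 38.75, rounded up to 39
- in total: 2 x 39 = 78 (equally, 62/0.80 = 77.5, rounded up to 78)

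**Step 3. Expected completers under 20% dropout.**

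| Randomised per arm | Expected completers per arm | Reaches 31? |
|---|---|---|
| 37 (as stated) | 37 x 0.80 = 29.6 | no |
| 38 | 38 x 0.80 = 30.4 | no |
| 39 | 39 x 0.80 = 31.2 | yes |

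In total, 74 x 0.80 = 59.2 against the required 62.

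**Step 4. Dropout that 37 per arm can absorb.** 1 - 31/37 = 6/37 = 16.2%. That is six losses per arm, where 20% of 37 is 7.4.

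**Step 5. Effect on power.** For a fixed effect, the expected test statistic scales with the square root of the sample size. At 80% power and two-sided 5% it equals 1.960 + 0.842 = 2.8016 (before rounding of the two terms). If n0 per arm gives exactly 80%, power at n per arm is Phi(2.8016 x sqrt(n/n0) - 1.96).

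- n0 = 31, n = 29.6: Phi(2.8016 x sqrt(29.6/31) - 1.96) = 78.2%
- n0 = 31, n = 29: 77.3%; n = 30: 78.7%
- n0 = 30, n = 29.6: Phi(2.8016 x sqrt(29.6/30) - 1.96) = about 79.5%

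The last line covers the case in which 31 was rounded up from a value only just above 30. The loss therefore lies between about 0.5 and 1.8 percentage points.

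**The case against.** The arithmetic itself is hard to dispute. The stronger objections concern its consequence.

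**Dropping out is not the same as leaving the analysis.** The intention-to-treat set keeps withdrawn children who still have outcomes, the diary records pain intensity every week, and multiple imputation is planned. A child who abandons the diet but reports at week 4 still counts. This stands in part: 29.6 is the expected number only if each dropout lacks a week-4 outcome, and some information may be recovered. But imputation does not restore an unobserved week-4 response. The Sample size section claims no credit for it and treats dropouts as lost to the required 31; that is why it adds children at all. The per-protocol set gains nothing from this argument.

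**The power figure depends on an unverifiable 31.** This also stands. The section gives only a 30% difference ("We assumed a 30% difference as being a clinically significant primary endpoint"), with no control rate or standard deviation, so 31 cannot be checked. For that reason power is given above as a range under stated assumptions. The dropout step is wrong whatever produced the 31.

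**The 20% may mean 20% of 31.** A dropout rate is ordinarily a share of those enrolled, and the article defines it no other way. Even on this reading, 37.2 rounds up to 38.

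**The gap is too small to matter.** It is two children per arm and at most about two points of power. This is a fair comment on its weight, not a defence of the figure.

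**Conclusion.** The concern holds. The figures 31, 20% and 37 are mutually inconsistent: the correct number is 39 per arm (78 in total), and the stated 37 falls short by two per arm. At the anticipated dropout the trial expects 29.6 evaluable children per arm. Power is then about 78% if 31 gives exactly 80%, and about 79.5% at best, so below the stated 80% in either case.

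This rests on taking 31 as correct, on reading dropout as a share of those randomised, and on dropouts having no week-4 outcome. The error biases no estimate or test and does not threaten the trial. It is nevertheless a plain mistake in the number that sets the recruitment target, and it should be corrected.

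**What to change.** Either of two corrections is enough.

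1. **Keep 74 and restate what it delivers.** The Sample size section would say that 37 per arm retains 31 evaluable children if dropout does not exceed about 16%, and that at 20% dropout about 29 to 30 per arm are expected, with about 78% power if 31 gives exactly 80%. This costs one line and leaves recruitment and the abstract's total unchanged.

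2. **Raise the target to 39 per arm, 78 in total.** This costs four more children and a change to the abstract. The Protocol amendments section requires a formal amendment with ethics committee approval for a change in sample size. With the fixed blocks of four described under Sequence generation and allocation concealment, 78 is 19.5 blocks (74 is likewise 18.5), so exactly equal arms are not guaranteed.

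Under either option the DSMB reviews at 25, 50 and 75% need no rewording, because they are stated as percentages without counts.

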### Assignment of interventions

#### Sequence generation and allocation concealment

Randomization will be based on a computer-generated randomization list developed by an independent investigator with no clinical involvement in the trial. The random numbers will be generated in blocked randomization (using a random block of 4: 2 subjects in group A and 2 in group B) with a 1:1 allocation ratio to ensure good balance between participant characteristics in both groups. The randomization sequence will be created using StatsDirect statistical software. Stratification will not be performed.

Allocation concealment will be ensured using opaque, sealed, numbered envelopes. The data regarding intervention assignments will be stored in a sealed envelope in a safe in the administrative part of the department. An independent person will open the next consecutively number envelope. Information about allocation of each participant will be given to the dietitian. The dietitian will develop a meal plan for each enrolled participant following the allocation. Each meal plan will contain the full name and address of the child. The meal plans will be provided to the catering company. The catering company will not be informed about the type of diet, and no suggestive information will be attached to the all-day box-diet provided to the participant.

After performing the data analysis, code numbers will be opened by the research coordinator (AH). In case any medical problem occurs for which treatment allocation is needed, the code can be broken by a principal researcher (AH, HS).

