#### Consent or assent

Written informed consent will be obtained from all participants before enrollment. The research dietitian will have a discussion with child and the child’s caregiver and answer any questions regarding the study. For children ≥13 years of age, the participants themselves can sign the informed consent; for younger children, two copies of the written informed consent will be obtained from the child’s caregiver.

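### A fixed block size of 4 in a single list, with every allocation passed to the dietitian who on the natural reading also leads the consent discussion, leaves about a third of upcoming allocations deducible.

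*Protocol article*

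**What the plan says.** The section Sequence generation and allocation concealment gives one block size and its exact make-up: "using a random block of 4: 2 subjects in group A and 2 in group B", "with a 1:1 allocation ratio". It adds that "Stratification will not be performed". Trial design describes a single-centre trial, so all children are drawn from one running list.

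The same section describes a list prepared by an independent investigator, and opaque, sealed, numbered envelopes opened in order by an independent person. It then states: "Information about allocation of each participant will be given to the dietitian". The Blinding section says that the dietitian stays unblinded. It separates the dietitian from the outcome assessor and the analysts, and mentions no separation from recruitment or consent.

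Under Consent or assent, for the conversation that precedes written consent: "The research dietitian will have a discussion with child" and the caregiver. Under Study procedure and timeline, the research dietitian also sees the family at Visit 0, where a dietitian explains the study with its risks and benefits and takes a detailed dietary history.

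**The concern.** With a known constant block size, anyone who has seen the earlier allocations can deduce some of the later ones. Once one arm has used both of its places in a block, the rest of that block is fixed. Envelopes hide what is inside them, but not what can be inferred from the envelopes already opened.

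Here the role that receives every allocation appears also to be the one that talks to the next family before they agree to join. Someone who expects a particular diet for the next child could, even without intent, present the study more or less warmly, or let a hesitant family go. The two groups could then differ at entry. Blinding participants, assessors and analysts acts after enrolment and cannot undo such a difference.

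**Working it through.** The documents state no predictability figure, so there is none to reproduce.

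**Inputs**
- Block of 4, two per arm, 1:1, one list (Sequence generation and allocation concealment).
- One centre (Trial design).
- 74 children (abstract, Methods), 37 per arm (Sample size).
- Recruitment over 24 months (Study settings and recruitment): 74 / 24 = 3.1 children a month, so earlier allocations would usually be known before the next family is approached.

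**Certain allocations per block of 4**

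There are 6 equally likely orders: AABB, ABAB, ABBA, BAAB, BABA, BBAA. An allocation is certain when one arm already has its two places.
- Positions 1 and 2: probability 0.
- Position 3: certain only after AA or BB, 2/6 = 1/3.
- Position 4: always certain, 1.
- Sum: 4/3 per block, and (4/3) / 4 = 33.3%.

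**Over 74 children**

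74 = 18 × 4 + 2. The last two are taken as positions 1 and 2 of a further block and add nothing.
- Expected number certain: 18 × 4/3 = 24, and 24 / 74 = 32.4%.
- Possible range: 18 (fourth places only) to 36 (third places too).
- The number is 18 plus a binomial count with n = 18 and p = 1/3, which has mean 6 and SD √(18 × 1/3 × 2/3) = 2. The simulated 95% range is 20 to 28.

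**Best guess (name the arm that is behind)**
- Probability correct by position: 1/2, 2/3, 1/3 × 1 + 2/3 × 1/2 = 2/3, and 1.
- Per block: 17/6 = 2.833 of 4, or 70.8%.
- Over 74: 18 × 17/6 + 1/2 + 2/3 = 52.17, and 52.17 / 74 = 70.5%, against 50% by chance.

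**Effect of changing the blocks**

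The varying-block share of certain allocations was simulated over 74 children, with an observer who knows which sizes are in use but not their order.

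| Scheme | Certain | Best guess correct |
|---|---|---|
| Fixed 4 | 32.4% (24 of 74) | 70.5% |
| Fixed 6, per full block | 25% | 68.3% |
| Random 4 or 6 | 5.6% (about 4 of 74) | 69.1% |

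The last best-guess figure agrees with a direct calculation on full blocks. A block of 6 yields 4.1 correct guesses, so an equal mix gives (2.833 + 4.1) / (4 + 6) = 69.3%. Varying the size removes most of the certainty but little of the guessing advantage.

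**The case against.** The strongest reply has four parts.

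- **Identity of the dietitian.** The documents never say outright that the research dietitian at consent and Visit 0 is the unblinded dietitian of the Blinding section. This stands as an assumption. It is the natural reading, because no second dietitian is described.
- **Control over entry.** A reader might infer that the dietitian decides who is eligible. The documents do not support that. A gastroenterologist makes the diagnosis, a nurse does the growth assessment, a physician judges concurrent medication, and most criteria are fixed thresholds or medical findings. The exposed channel is the consent discussion and the baseline dietary contact, which is narrower.
- **Conditions for certainty.** The 32% requires someone who knows the block size, tracks the list from its start and has each allocation before meeting the next family. With one site, one list and about three children a month this is feasible, but nothing shows that it happens. Publication of the block size adds little, because the article is dated January 2021 and recruitment was planned from September 2020.
- **Existing safeguards.** The independent list-maker, the opaque envelopes and the independent opener are real protections against tampering. They do not stop deduction from past allocations.

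The word random in the description of the block might be taken to mean varying sizes. Only one size is given, with its exact composition, so that reading does not hold.

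**Conclusion.** The point holds as a design weakness that is cheap to correct. With a fixed block of 4, about 24 of 74 allocations (32% on average, 95% range 20 to 28 allocations) are deducible with certainty, and the best guess succeeds about 70% of the time. This rests on two assumptions: that the dietitian who receives allocations is the one who discusses consent, and that this person knows the block size and follows the sequence.

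Two stronger conclusions might be drawn, and neither is supported. The first is that a third of allocations will in fact be known at consent: the figure measures what could be deduced, not what anyone does. The second is that the trial's groups are or will be biased: the documents show an exposure at the consent step and no more. Nor does the point imply that the trial should be stratified, since stratification would not address predictability.

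**What to change.** Make two changes together.

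1. Have the independent list-holder generate the remaining sequence with randomly varying block sizes, for example 4 and 6, and withhold the sizes and their order from all site staff, including the dietitian. Over a full 74-child list this would bring certain allocations from about 32% to about 6%; the gain in practice applies only to children not yet randomised.
2. Because the best guess would still be right about 69% of the time, have the consent discussion, including the explanation of risks and benefits, led by an existing team member who does not see allocations. The dietitian can continue the dietary assessment and meal planning. If a different, blinded dietitian already handles consent, the protocol should say so, and this second change is then not needed.

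The cost is a new list and a new set of envelopes, one conversation moved to another team member, and slightly less exact balance in numbers: at any moment the arms could differ by up to 3 (half of 6) instead of 2 (half of 4). No analysis or sample size changes. Under the protocol's own rule on amendments, a change to study procedures needs ethics committee approval before it is put into effect.

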#### Eligibility criteria

##### Inclusion criteria

At enrollment, the volunteer children must fulfill all of the following eligibility criteria to be considered for inclusion: (1) age at least 8 years and ≤ 18 years (regardless of race, ethnicity, gender); (2) FAP-NOS or IBS diagnosed according to the Rome IV Criteria [2]; (3) baseline average pain intensity at least 30 mm on a 100-mm Visual Analogue Scale (VAS) [9]; (4) feeding via the oral route; (5) ability to read and comprehend any employed questionnaires/scales; (6) signed informed consent; and (7) stated availability throughout the study period.

Participants with IBS and a stool consistency score > 5 on the Bristol Stool Scale will be classified as having IBS with predominant diarrhea (IBS-D); if the stool consistency score is < 3, the subjects will be classified as having IBS with predominant constipation (IBS-C) [16].

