#### Methods of additional analyses

Both the primary and secondary outcomes will be analyzed by logistic regression, controlling for three, prespecified, potential confounding variables, i.e., age, sex, and subtype of IBS. The difference between study groups will be considered significant when the *p* value is < 0.05, when the 95% CI for RR (or odds ratio [OR]) does not include 1.0, or when 95% CI for MD does not include 0. All statistical tests will be two-tailed and performed at the 5% level of significance.

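### Unstratified blocks of 4 balance the numbers per arm, not participant characteristics, so the IBS/FAP-NOS split is left to chance although each subtype is to be assessed separately; the cost is modest

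*Protocol article*

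**What the plan says.** All references are to the protocol article.

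- **Sequence generation and allocation concealment:** one computer-generated list in blocks of four, two children to each arm. The text describes this as blocking "with a 1:1 allocation ratio to ensure good balance between participant characteristics in both groups". The same paragraph ends: "Stratification will not be performed".
- **Inclusion criteria:** two diagnoses are enrolled, "FAP-NOS or IBS diagnosed according to the Rome IV Criteria". Children with IBS may be further classed as IBS-D or IBS-C by stool consistency.
- **Study procedure and timeline:** the gastroenterologist makes the diagnosis at Visit 0, and randomization follows.
- **Abstract, Methods:** "Seventy-four children aged 8 to 18 years with a FAPD" are to be randomized, and "Each FAPD subtype will be assessed separately".
- **Data analysis:** the group comparisons (t, Mann-Whitney, chi-square or Fisher tests) are unadjusted.
- **Methods of additional analyses:** a logistic regression "controlling for three, prespecified, potential confounding variables, i.e., age, sex, and subtype of IBS".

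**The concern.** The stated purpose and the stated method do not match. A permuted-block list fixes the count of A and B within every four consecutive children and knows nothing else about them. It keeps arm sizes close. It gives no more control over diagnosis, age or sex than any other randomization with equal arms. Control over a characteristic at allocation needs stratification or minimization, and the protocol rules stratification out.

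This matters most for diagnosis. The trial pools two diagnoses, commits to assessing each one, and knows each child's diagnosis before allocation. Two things are at stake: the precision of the within-subtype comparisons, and chance imbalance in subtype in the pooled unadjusted comparison.

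**Working it through.** **Inputs from the protocol.** N = 74 (37 per arm), 1:1, fixed blocks of 4, one list. The protocol gives no figure for subtype balance, so there is none to reproduce. It also gives no expected subtype mix. The number m of children with FAP-NOS is therefore an assumption, taken over the range 15 to 37.

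**Step 1: what the list controls.** 74 = 18 × 4 + 2, so the arms end within 2 children of each other. The assignments do not depend on subtype. The number of FAP-NOS children in one arm is then close to hypergeometric (m drawn over 37 and 37), and the SD of the between-arm difference in count is about 2 × √[m × ¼ × (74 − m)/73]. For m = 25 this is 2 × √(25 × 0.25 × 49/73) = 4.1 children.

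**Step 2: how often imbalance occurs.** Simulated block lists (40,000 for each m, subtype order random) give the chance that the FAP-NOS share differs between arms by at least the stated amount:

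| FAP-NOS children (assumed) | ≥10 points | ≥15 points | ≥20 points |
|---|---|---|---|
| 15 | 25% | 8% | 3% |
| 20 | 39% | 17% | 7% |
| 25 | 33% | 17% | 6% |
| 30 | 43% | 21% | 8% |
| 37 | 40% | 19% | 8% |

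The columns do not rise smoothly because the counts are whole numbers. With m = 25, a split of 15:10 or worse occurs in about 33% of trials and 17:8 or worse in about 5%; the hypergeometric gives the same figures. A 2:1 split or worse occurs in about 25% of trials at m = 15, but only about 7% at m = 20 and 5% at m = 25.

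**Step 3: what an uneven split costs within a subtype.** With a and b children in the two arms and m = a + b, the efficiency relative to an even split is 4ab/m².

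- 15:10 gives 4 × 15 × 10/625 = 0.96.
- 17:8 gives 4 × 17 × 8/625 = 0.87.
- 10:5 gives 4 × 10 × 5/225 = 0.89.

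Averaged over the simulated trials, efficiency is about 97% at m = 25 and 95% at m = 15.

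**Step 4: what imbalance does to the pooled comparison.** The shift in the observed difference is roughly the imbalance in share times the difference in response between subtypes. The documents do not give the latter. As an illustration with assumed figures, 15 points × 20 points = 3 points, and 20 × 30 = 6 points. The standard error of a risk difference with 37 per arm at 50% response is √(2 × 0.25/37) = 11.6 points.

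**Step 5: with stratification.** Separate blocks of 4 within IBS and within FAP-NOS limit the difference within a subtype to 2 children, reached only in an incomplete last block. In simulations with an assumed IBS share of 50%, 65% or 80%, no stratified trial reached a 10-point difference, and overall arm sizes still ended within 2.

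**The case against.** The strongest reply is that declining to stratify is an accepted, openly stated choice in a small single-center trial. The sample size supports only the pooled comparison, and the commitment to subtypes is one sentence in the abstract with no power claim. An uneven split costs little, as Step 3 shows; the small size of a subtype limits its analysis more than its split does. A regression with a subtype covariate is already prespecified.

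Most of this stands, and it rules out some stronger readings. A reader might infer that the subtype comparisons would be biased or the primary test invalid. Neither follows: allocation within a subtype is still random, and chance imbalance is already part of the error rate of the unadjusted tests. Nor do the documents show that IBS and FAP-NOS differ in prognosis or response, so a material distortion of the pooled result cannot be claimed.

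Two parts do not stand. The choice may be legitimate, but the property claimed for it is untrue. And the regression is partial protection only. It is an additional analysis, and its covariate refers to subtype within IBS. Read with the IBS-D and IBS-C definitions under Inclusion criteria, that does not clearly separate IBS from FAP-NOS. A model fitted to all children would need a category for FAP-NOS, and the text does not say so.

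**Conclusion.** The point holds in limited form. The protocol attributes to blocking a balance of characteristics that blocking does not give, and leaves the IBS/FAP-NOS split to chance while promising to assess each subtype. Differences in share of 10 points or more would be common (about 25-43% of trials) and of 20 points or more uncommon (about 3-8%), on the assumption that 15 to 37 of the 74 children have FAP-NOS. The consequence is a modest loss of precision within subtypes and a chance imbalance in the pooled comparison that matters only if subtype is prognostic, which the documents do not establish. It is worth correcting because the statement is wrong and the remedy is cheap, not because the trial's validity is at risk.

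**What to change.** 1. Generate two permuted-block lists with two series of sealed envelopes, one for IBS and one for FAP-NOS. Diagnosis is already available at Visit 0.
2. Reword Sequence generation and allocation concealment to say that blocking balances the numbers per arm and stratification balances subtype. Delete the claim about characteristics in general.
3. In Methods of additional analyses, change the third covariate to FAPD subtype (IBS v FAP-NOS), so that it matches the randomization. The present wording should be changed, not kept.

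The cost is one more envelope series, one more possible incomplete block, and a short protocol change, which needs ethics approval under Protocol amendments because it affects study design. Two strata in 74 children do not create sparse strata over the range considered. If the list can no longer be changed, make changes 2 and 3 only, with the reworded sentence saying simply that blocking balances numbers.
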